#### 2.3.6. Withdrawal Criteria

Participants will withdraw from the trial if (1) poor subject compliance; (2) allergic to therapeutic medicine; (3) cases lost to follow-up in the trial; (4) patients request to withdraw from the trial; (5) cannot meet the inclusion criteria after inclusion; and (6) serious diseases or complications occur suddenly during the trial that has no causal relationship with AKI. Participants developing serious diseases or complications during the treatment cannot be withdrawn until the assessment of causal relationship with AKI has been accomplished. Complications such as cardiorenal syndrome and sepsis usually indicate the progression of AKI and should not be simply excluded from the efficacy analysis. Reasons should be given for withdrawal cases, and related forms should be reserved for future reference. Those cases are not statistically analyzed for efficacy, but adverse reactions should be analyzed for those who have received at least one treatment and can be determined to have records of adverse reactions. Participants who withdraw within two weeks after treatment will be defined as missing case and will not be enrolled in the pee-protocol population.

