### 2.4. Randomization and Blinding

A simple random method is adopted, and SPSS (version 21.0) software will be used by independent biostatisticians to generate random number sequences. Written informed consent should be signed immediately by himself/herself, agreeing to voluntarily enroll in the trial. Participants should be consented for randomization and participation. According to the sequence of enrolling in clinical observation, participants will be randomly numbered and divided into the RG group, the CHF group, and the RG + CHF group by investigators at 1 : 1 : 1 ratio. During randomization producer, sealed envelopes marked with sequential coding numbers will be adopted to keep allocation details, and group allocation should be kept blind to patients, biostatisticians, and investigators. As placebo is not used in the control group, it is not possible to be blind in the treatment. However, it is masked from staff performing all laboratory investigations.

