### 2.9. Sample Size Estimation

The sample size will be calculated according to the primary outcome of baseline Scr change. Based on previous studies and literature reports [26, 30], the mean value of Scr was 160.39 *μ*mol/l, and the standard deviation was 44.43 *μ*mol/l. We thus hypothesize that Scr for CHF combing RG group would be significantly lower than the other two groups by more than 30 *μ*mol/l. It is calculated using the sample size estimation software PASS (version 15.0.3) to achieve test efficacy 1–*β* = 0.90 and significant difference *α* = 0.05 (one-sided test). Considering 20% drop rate, the estimated sample size for randomization will be 54 cases in each group for a total of 162 cases.

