### 2.10. Statistical Analysis

The principal analysis will be conducted on a full analysis set (FAS), which consists of participants randomly allocated into two groups. Participants completing and complying well with the study protocol without major violation will be referred to the per-protocol population. All participants taking test drugs will be enrolled in safety analysis and conform with the ITT principle.

For non-normally distributed variables, mean ± standard deviation or median will be brought to describe continuous variables. Categorical variables will be presented in the form of numbers and percentages. The difference in Scr will be tested using the one-way ANOVA with repeated measures. The secondary outcomes will be compared between two groups using the independent-samples Student's *t*-tests for normally distributed continuous data and using Pearson's chi-square test (or Fisher's exact test if cell count <5 in any cell) for categorical data. Two-sided tests will be used for all statistical tests, and *P* < 0.05 will be considered statistically significant. SPSS (version 21.0) software will be used to carry out statistical analysis by a biostatistician not involved in the study. No additional analyses or interim analysis will be performed.

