### 2.12. Safety Assessment

In this trial, AEs are recognized as negative or untoward medical manifestations during the study conducting period, regardless of the possibility of a causal relationship. CHF has been applied to clinical treatments and animal experiments for many years and proved an effective prescription, and no obvious AEs have been observed. According to the package insert of RG, it may have skin rash and other allergic symptoms such as anorexia, nausea, upper abdominal discomfort, and other gastrointestinal symptoms occasionally. Relevant AEs occurring in this trial will be recorded systematically in detail throughout the trial. Meticulous description of event cause, subsequent interventions, handling outcome, and other relevant information will also be included in the form. If AEs occur, the patient will be closely observed and properly taken care of until AEs disappear. It is essential to carry out follow-up investigations. Besides, the results should be recorded in detail and then reasons will be analyzed. Serious adverse events (SAEs) are as follows: (1) critical or life-threatening complications; (2) hospitalization or disability, even death; and (3) other serious event significant hazards to participants. AEs and SAEs will be monitored and evaluated by researchers, and then, researchers will give related participants proper treatments and report them to authorities. They will also be reported in trial publications at the end of the study.

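### Sections 2.3.6 and 2.10 give conflicting rules for which withdrawn patients enter the safety analysis, and the 2.3.6 rule depends on the outcome

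*Protocol article*

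**What the plan says.** Three places in the protocol article bear on who and what is counted for safety.

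- **2.3.6, Withdrawal Criteria.** Withdrawn cases are left out of the efficacy analysis. For safety, "adverse reactions should be analyzed for those who have received at least one treatment and can be determined to have records of adverse reactions". The reasons for withdrawal include "2) allergic to therapeutic medicine; (3) cases lost to follow-up in the trial", and also serious illness arising during the trial with no causal link to AKI.
- **2.10, Statistical Analysis.** "All participants taking test drugs will be enrolled in safety analysis and conform with the ITT principle". No condition is attached about having an event.
- **2.12, Safety Assessment.** AEs are defined "regardless of the possibility of a causal relationship", and "Relevant AEs occurring in this trial will be recorded systematically in detail throughout the trial".

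Section 2.9 supplies the arm size and the drop-out allowance: "Considering 20% drop rate, the estimated sample size for randomization will be 54 cases in each group for a total of 162 cases".

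**The concern.** The clause in 2.3.6 joins two conditions with an 'and': the withdrawn patient was treated, and has a record of a reaction. A treated patient who withdraws with no recorded reaction is therefore inside the safety analysis under 2.10 and outside it under 2.3.6. The document gives no order of precedence, and 2.3.6 is the section written specifically for withdrawals, so an analyst could follow it in good faith.

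If that happened, a withdrawn patient would enter the denominator only by having the event. The event type differs too. An unrelated illness that leads to withdrawal is an AE under 2.12 but need not be an adverse reaction under 2.3.6, so it could go uncounted.

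Safety is one of the two stated aims in 2.1, and the planned drop-out of one patient in five is large enough for the choice of rule to show in the reported rates.

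**Working it through.** **Plan's own figures.** The article gives no AE rate and no safety denominator, so there is no safety figure to reproduce. The arm size used below can be reproduced: a three-group one-way ANOVA F test with means m, m and m − 30, an SD of 44.43, alpha 0.05 and power 0.90 needs 43 per arm (power 0.9025), and 43/(1 − 0.20) = 53.75, rounded up to 54. This confirms the input and has no other bearing on the point.

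**Inputs.**
- From 2.9: n = 54 per arm, withdrawn share d = 0.20.
- Assumed: all 54 were treated, and every drop-out is a treated withdrawal.
- Assumed: true AE rate p in retained patients, q in withdrawn patients. The article gives neither, so a range is shown.
- r = share of withdrawn patients' events that count as adverse reactions under 2.3.6.

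**Formulas.**
- Under 2.10: rate = [n(1 − d)p + n·d·q] / n.
- Under literal 2.3.6: rate = [n(1 − d)p + n·d·q·r] / [n(1 − d) + n·d·q·r].

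Retained: 54 × 0.80 = 43.2. Withdrawn: 54 × 0.20 = 10.8.

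**Step 1. Same rate in withdrawn and retained (q = p), all events counted (r = 1).**

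| True rate (2.10) | Literal 2.3.6 | Reported |
|---|---|---|
| 5% | 2.7/43.74 | 6.2% |
| 10% | 5.4/44.28 | 12.2% |
| 20% | 10.8/45.36 | 23.8% |
| 30% | 16.2/46.44 | 34.9% |

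The relative excess runs from about 23% at a true 5% to about 16% at a true 30%.

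**Step 2. Unrelated events in withdrawn patients not counted (p = q = 10%, so 1.08 events among the withdrawn).**
- Half count (r = 0.5): (4.32 + 0.54)/(43.2 + 0.54) = 4.86/43.74 = 11.1%.
- None count (r = 0): 4.32/43.2 = 10.0%, with no bias.

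**Step 3. More events among the withdrawn (p = 10%, q = 50%).** The rate over all treated is (4.32 + 5.4)/54 = 9.72/54 = 18.0%.
- All count: 9.72/(43.2 + 5.4) = 9.72/48.6 = 20.0%, overstated.
- None count: 4.32/43.2 = 10.0%, understated.

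The direction therefore depends on how many of the withdrawn patients' events are classed as reactions.

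**Step 4. Comparison between arms (r = 1, q = p).**
- Equal withdrawal and equal true rates: every arm shifts alike, and a null difference stays null.
- Equal withdrawal at 20% with true rates of 10% and 20%: the gap reads 23.8 − 12.2 = 11.6 points instead of 10.
- Withdrawal of 10% in one arm and 30% in another (assumed), true rate 10% in both: 5.4/49.14 = 11.0% against 5.4/39.42 = 13.7%.
- The same withdrawal, true rate 20% in both: 10.8/49.68 = 21.7% against 10.8/41.04 = 26.3%.

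**The case against.** The strongest reply is that the statistical section already holds the standard definition. Section 2.10 admits everyone who took study drug. Section 2.3.6 sits among the withdrawal criteria and names no analysis set, denominator or rate. If 2.10 governs, the distortion is zero. This stands in part: it rules out presenting the 2.3.6 clause as the trial's settled safety rule. It does not remove the conflict, because the article does not say that 2.10 prevails.

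A second reply is that the clause is awkward English and may mean only that usable safety records exist for the patient, or that reactions recorded before withdrawal must still be reported. Either reading is possible, and neither would remove reaction-free patients from a denominator. But the words refer to records of reactions, and even the first of these readings adds a condition that 2.10 lacks.

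A third reply is that 2.12 promises recording and publication of AEs without limiting this to completers, so one loose use of 'reaction' should not override it. That is fair, and it makes the event-type mismatch the weaker half of the point.

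A reader might also infer that the rule distorts the comparison between arms, or always inflates rates. The documents support neither. The article gives a single drop-out figure and none by arm, and Step 2 and Step 3 show that the bias can vanish or reverse.

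**Conclusion.** The point holds as an internal contradiction. Sections 2.3.6 and 2.10 give different rules for withdrawn patients in the safety analysis, and 2.3.6 and 2.12 use different event terms. It should be corrected, but it is of moderate to low weight because 2.10 already contains a sound definition.

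The size is conditional. If 2.3.6 were followed literally, with 20% withdrawn, every event counted and the same event rate in withdrawn and retained patients, true rates of 10% and 20% would be reported as about 12.2% and 23.8%. If unrelated events in withdrawn patients are dropped, the excess is smaller or absent, and the rate can be understated where withdrawn patients have more such events. The AE rates are assumptions; only the arm size and the drop-out come from the article.

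Distortion between arms requires withdrawal or event patterns to differ by arm. That is plausible, since 2.4 concedes that treatment cannot be blinded and 2.5 gives the arms a daily infusion, an oral drug plus enemas, or both. The article does not state it.

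**What to change.** Make 2.3.6 agree with 2.10. Replace its clause on adverse reactions with: *every withdrawn participant who received at least one study treatment remains in the safety analysis, whether or not an adverse event was recorded, and all AEs as defined in 2.12 are counted.*

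The mention of the ITT principle in the safety sentence of 2.10 fits poorly with a set defined by drug taken. It can also be read as meaning that no treated participant is dropped, so removing it is optional tidying.

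The cost is one reworded clause, with no added patients, visits or data. Whether reported rates would be higher or lower than under the literal 2.3.6 rule cannot be told in advance.

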#### 2.3.7. Shedding Criteria

Natural shedding and loss of follow-up during observation may occur during the trial. He/she will quit by himself/herself if it is not suitable to continue participating in the trial because of severe complications or unpredictable events. Shedding cases should be documented in detail, and intention-to-treat (ITT) analysis should be performed in the end.

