### 2.5. Interventions

Patients diagnosed with CKD stages 2–4 complicated with AKI grades 1–2 will be enrolled after signing written informed consents. They will be randomly divided into the RG group, the CHF group, and the RG + CHF group. To minimize potential loss and help participants conduct the trial smoothly, three group patients will receive study behavior and health education, and they will also be told possible risks and benefits, their rights and obligations, and how to handle an emergency situation. All patients will receive a low-salt, high-quality, and low-protein diet (protein intake 0.6–0.8 g/kg/d). Also, they will receive general treatments, whose purposes are to correct water, electrolyte, and acid-base balance disorders, control blood pressure, improve anemia, and correct renal bone diseases. Designed investigations will keep in touch with participants regularly and assist them to receive treatment and testing on schedule.

The RG group will be given RG 1.8 g added to 0.9% normal saline or 5% glucose 250 ml for injection, intravenous injection (IV), once per day for 2 weeks. The CHF group will be given CHF orally, twice per day for 2 weeks. At the same time, the concentrated solution of CHF will be given an enema, once per day for 5 days, and then rest for 2 days, 5 times in a week. The RG + CHF group will be the combination of the RG group and the CHF group, and intervention methods are the same as the above.

Pharmaceutical compositions of CHF are mainly as follows: prepared rhubarb (Zhida Huang), Ligusticum wallichii (Chuan Xiong), Codonopsis pilosula (Dangshen), Coptidis rhizome (Huanglian), Smilacis glabrae (Tufuling), etc. RG will be produced by Chongqing Yaoyou Pharmaceutical Co. Ltd., and CHF will be produced by Jiangyin Tianjiang Pharmaceutical Co. Ltd. Therefore, the quantity and quality of medicine can be effectively guaranteed.

Related examinations will be conducted and collected at baseline, every 1 week during treatment. Patient information will be recorded, and efficacy-related examinations, mechanism-related indicators, safety-related indicators, and drug management will be closely observed. Measured items and time points are listed in Table 3.

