**RG group**			
**CHF group**			
**RG** **+** **CHF group**			
Effectiveness observation			
**Renal functions (Scr, BUN, eGFR)**	×		×
**AKI biomarkers (NGAL, IL-18, *γ*-GT)**	×		×
**TCM symptoms**	×		×
Mechanism observation			
**Inflammatory indicators (IL-6, TNF-*α*)**	×		×
**Oxidative stress indicators (HO-1, MDA, SOD)**	×		×
Safety observation			
**Electrocardiogram**	×		×
**Blood routine**	×		×
**Urine routine**	×		×
**Fecal routine and occult blood test**	×		×
**Serum potassium**	×		×
**Hemoglobin**	×		×
**Adverse events**		×	×
Drug management			
**Drug distribution**	×	×	×
**Drug recycling**		×	×
**Drug count**		×	×
Research conclusion			×

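### Withdrawal for treatment or eligibility reasons ends trial participation and bars the patient from efficacy analysis, and Table 3 schedules no post-baseline Scr before week 2, which conflicts with the promised ITT/FAS analysis

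*Protocol article*

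**What the plan says.** **Withdrawal (2.3.6).** The list opens: "Participants will withdraw from the trial if (1) poor subject compliance; (2) allergic to therapeutic medicine". It also includes ineligibility discovered after inclusion and the case where "serious diseases or complications occur suddenly during the trial that has no causal relationship with AKI". Loss to follow-up and the patient's own request stand in the same list with the same consequence. For withdrawn participants the section states: "Those cases are not statistically analyzed for efficacy". It then adds: "Participants who withdraw within two weeks after treatment will be defined as missing case", and keeps those participants out of the per-protocol population. AKI-related complications are treated differently: they "usually indicate the progression of AKI and should not be simply excluded from the efficacy analysis".

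**Shedding (2.3.7).** Participants may also quit because of severe complications, here without the limit to causes unrelated to AKI. The section ends: "Shedding cases should be documented in detail, and intention-to-treat (ITT) analysis should be performed in the end".

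**Analysis set (2.10).** The principal analysis is on a full analysis set (FAS) of randomised participants. Scr is tested by repeated-measures ANOVA.

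**Schedule.** Section 2.5 says: "Related examinations will be conducted and collected at baseline, every 1 week during treatment", and refers to Table 3 for items and times. In Table 3 the row "Renal functions (Scr, BUN, eGFR") is marked at week 0 and week 2. Its week-1 cell is blank, and the table has no column for early termination.

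**The concern.** The protocol draws no line between stopping study drug and leaving the study. A patient with an allergic reaction on day 4, or one who misses enemas, has not refused a blood test at week 2. Under 2.3.6 that patient is nevertheless out of the trial and out of the efficacy analysis. If Table 3 is followed, the record holds a baseline Scr and nothing after it.

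The ITT/FAS analysis then lacks outcomes that could have been observed. An analysis plan can choose an estimator but cannot recover a sample that was never taken. Classical repeated-measures ANOVA uses only patients with complete measurements, so an FAS defined as all randomised would in practice shrink to completers.

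The loss need not be balanced. The arms receive a daily infusion, an oral drug plus enema, or all three (2.5), and treatment is not blinded (2.4). Stopping for compliance or allergy can plausibly differ by arm and be related to response. The drop-out allowance in the sample size protects precision. It does nothing against this bias.

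**Working it through.** **1. The passages side by side**

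| Place | Patient who stops drug before week 2 |
|---|---|
| 2.3.6 | Withdrawn from the trial, not analysed for efficacy; early leavers labelled missing |
| 2.3.7 | ITT analysis required |
| 2.10 | In the FAS by virtue of randomisation |
| Table 3 | No Scr between week 0 and week 2 |
| 2.5 | Weekly examinations, with items and times left to Table 3 |

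The first row cannot stand with the second and third. The last two need reconciling.

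**2. The plan's own figure**

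Inputs from 2.9: difference 30 µmol/l from each of the other two groups, SD 44.43 µmol/l, power 0.90, α 0.05, 20% drop-out.

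- A three-group ANOVA with means (30, 30, 0) has mean 20 and deviations 10, 10 and −20.
- f = √((100 + 100 + 400)/3)/44.43 = 14.14/44.43 = 0.318.
- This needs 43 per group (power 0.9025), and 43/0.80 = 53.75, so 54 per group and 162 in total.

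The stated size is reproduced. The planned number absorbs the loss of precision from 20% drop-out.

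**3. How many patients could be affected**

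- 0.20 × 162 = 32.4, or 0.20 × 54 = 10.8 per arm (about 11).
- This is an upper bound, because the 20% also covers true losses to follow-up and refusals.

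**4. Size of the bias**

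Let p be the share of an arm without an outcome, and g the mean outcome of those lost minus that of those observed. The arm's full mean is the observed mean plus p × g. With equal p in two arms, the error in the observed contrast is p × (g₁ − g₂) in absolute value.

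Assumption: g₁ − g₂ is 0.5 to 1 SD, that is 22.2 to 44.43 µmol/l.

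| Drops that are treatment stops (assumption) | p | Bias, µmol/l | Share of 30 µmol/l |
|---|---|---|---|
| Half | 0.10 | 2.2 to 4.4 | 7% to 15% |
| All | 0.20 | 4.4 to 8.9 | 15% to 30% |

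**5. A second route**

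Suppose instead that g is the same in both arms and the drop-out shares differ. The bias is (p₁ − p₂) × g. For shares differing by 10 to 20 percentage points and g of 20 to 44.43 µmol/l (assumptions), it runs from 0.10 × 20 = 2.0 to 0.20 × 44.43 = 8.9 µmol/l. The order of magnitude is the same. With equal shares and equal g, the bias is zero.

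**The case against.** Several objections have force.

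- **The missing-case sentence partly defines the per-protocol set.** Such an exclusion is conventional there, and the two-week window could run from the start or the end of treatment. This is right. The firmer conflict with ITT is the separate sentence barring withdrawn cases from efficacy analysis, which does not depend on that reading.
- **Complications.** A reader might infer that any complication removes a patient from efficacy. Section 2.3.6 does not say so: it withdraws only for illness unrelated to AKI, requires causality to be assessed first, and protects AKI-related complications from simple exclusion. Section 2.3.7 has no such limit, so the two need reconciling.
- **Week-1 Scr.** A reader might infer that none will be taken. That rests on Table 3 alone, since 2.5 speaks of weekly examinations. If a week-1 Scr is taken, only those leaving before it lack a post-baseline value, but later leavers are still barred from efficacy.
- **Follow-up is not wholly absent.** Section 2.12 has patients with adverse events observed until resolution, and 2.5 has staff help participants keep to the testing schedule. Neither guarantees a week-2 Scr for someone already withdrawn.
- **A condensed article may omit detail.** This does not answer a rule that the article states outright.
- **The magnitude.** The whole 20% cannot be charged to this rule, hence the halved case. The 0.5 to 1 SD gap has no support in the documents, and 44.43 is taken here as the SD of Scr level, while the primary outcome is a change in slope. It would also be too strong to say that every absent value must be imputed, because likelihood methods need no explicit imputation.

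**Conclusion.** The point holds in this form: 2.3.6 ends trial participation for reasons that do not prevent a blood test and bars those patients from efficacy analysis. By Table 3, those withdrawn before week 2 have no scheduled post-baseline primary outcome. This contradicts the ITT analysis in 2.3.7 and the FAS in 2.10.

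The contradiction rests on the text alone. The size does not. Roughly 2 to 4.5 µmol/l if half of the drops are treatment stops, or 4.5 to 9 µmol/l if all are, depends on the assumed between-arm gap of 0.5 to 1 SD of Scr level. The direction cannot be determined from the documents. The documents do not show that 20% of patients will be lost through this rule, or that the loss will in fact differ by arm.

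**What to change.** - In 2.3.6, state that outcome collection continues whatever happens to study treatment. The scheduled week-2 Scr, BUN, eGFR and adverse-event assessment are obtained unless the participant withdraws consent to follow-up, and one Scr is requested from anyone who leaves.
- Remove the efficacy exclusion and the missing-case label as far as the FAS/ITT analysis is concerned. Keep the exclusion for the per-protocol set only.
- Make 2.3.6, 2.3.7 and 2.10 agree, including on severe complications.
- Reconcile 2.5 with Table 3, so that it is clear whether a week-1 Scr exists.

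No rule on when study treatment stops is proposed.

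The cost is protocol wording, a routine blood sample already scheduled for week 2, an exit sample for those who leave, and slight extra site effort to recall participants who stopped treatment. The ITT contrast may also be smaller than the completers' contrast. If stoppers gain nothing and stopping is equal across arms (assumptions), 30 µmol/l becomes 30 × 0.9 = 27 at 10% stopping and 30 × 0.8 = 24 at 20%. With outcomes on all 54 per arm, the ANOVA power is then 0.909 and 0.828.
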